### **Baseline Covariates considered for inclusion in referable retinopathy prediction model**

The covariates to be considered for inclusion into the model are those reported in the literature as predicting retinopathy risk OR have been included in previous risk models.

Time updated covariates will be used in the analyses being updated wrt each screening date

- Sex coded
- Ethnicity
- Current age
- Age at diagnosis
- Pt entry date
- The Scottish Index of Multiple Deprivation (SIMD) quintile- this is a residence based measure of socioeconomic status .
  
- BMI (kg/m^2)
- Height, m
- HbA1c mmol/mol (To reduce potential for reverse causation, HbA1c values are to be lagged by at least one year. Start by considering running mean of readings taken between 1 and 3 years prior to baseline.)
- eGFR
- Albuminuria status ( 1: Normal 2: Micro 3: Macro)
  
- Systolic blood pressure, mmHg
- Diastolic blood pressure, mmHg
- Treated hypertension (based on prescription of any blood pressure lowering drugs)
  
- Total cholesterol, mmol/L
- Log (total/HDL) cholesterol
- Also consider non-HDL cholesterol, HDL-c and LDL-c as a set of lipid variables, choosing the combination giving the best model fit?
- Treated elevated cholesterol - ie on Statin therapy or other lipid lowering drugs (No LLT, statins, other LLT)
  
- Smoking status (categorised as never smoked, ever-smoked, current smoker- we do not think our pack year data are reliable enough to use pack years )
  
- Screening status at last screening available
  - We will also construct a weighted average of screening scores from all preceding episodes

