### a. Poisson regression

We will use Poisson regression model with backward elimination but we may use a different link function to deal with the interval censoring - In addition we will evaluate the use of non-parametric methods for interval-censored survival analysis in place of the interval regression models.

All model fitting will be done on 70% of the data (selected randomly by patient, maintaining ratio of events), and the remaining 30% will be used for internal validation. We will randomly assign the individuals in the dataset into these two partitions.

We include current age, sex, and diabetes duration as our base set of covariates in our initial model and will then use backward elimination to drop variables from the model, using a reduction in AIC of  $< 2$  units as the selection/stopping criterion.

We will initially include a simple covariate of screening status at last screening as a covariate

We will then extend this to be a weighted score of all prior screenings weighted by how recent the measure is

The model will contain an offset term for the  $\log(\text{length of interval})$ .

We will also select across age and sex interaction terms for each covariate.

To be agreed : should we include any shrinkage/ penalizing?

*Assumption about linearity of effects of covariates :*

We will use backward elimination with multivariable fractional polynomials

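### The AIC threshold for backward elimination has no stated direction: read as a stopping rule on removal it can never drop a one-parameter term, and the age terms are linearly dependent

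*SAP*

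**What the plan says.** The SAP section on Poisson regression names the method: "We will use Poisson regression model with backward elimination but we may use a different link function". It then says "We include current age, sex, and diabetes duration as our base set of covariates in our initial model", and that the next step is "backward elimination to drop variables from the model, using a reduction in AIC of" less than 2 "units as the selection/stopping criterion".

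The same section widens the model in three ways:
- Screening history is added: "We will initially include a simple covariate of screening status at last screening as a covariate", later replaced by a recency-weighted score of all earlier screenings.
- Interactions enter the search: "We will also select across age and sex interaction terms for each covariate".
- Backward elimination is to be combined with multivariable fractional polynomials. No selection criterion is given for that step.

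The baseline covariate section lists the candidates: "The covariates to be considered for inclusion into the model are those reported in the literature as predicting retinopathy risk", or those used in previous risk models. Current age and "Age at diagnosis" are both on that list, and diabetes duration is in the base set.

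**The concern.** In backward elimination each step removes a term, so a criterion described as a stopping rule is naturally applied to the change in AIC on removal. On that reading the threshold of 2 equals the largest fall that removing a single parameter can produce. The rule would then keep every single-parameter covariate and interaction, including pure noise, while still removing terms with more parameters.

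The sentence can also be read in other ways that give very different models, and nothing in the section decides between them. It is the only numerical selection rule in the plan. The resulting model is scored on the 30% test set, receives the hidden Markov risk score, and may be the one that drives the comparison of screening numbers. Two analysts following the text could carry different models into all of that, and the choice between readings could be made after results are seen.

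The dependence among the age terms is a smaller fault in the same selection step: a model with all three linear terms is not of full rank.

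**Working it through.** **Inputs.** From the Poisson regression section: backward elimination; a threshold of less than 2 AIC units; its role as both selection and stopping criterion; a base set of current age, sex and diabetes duration. The section states no alpha or expected model size, so there is no derived figure to reproduce. The check is of what the threshold does.

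**Formula.** AIC = -2 log L + 2 x (number of parameters). For a term with k parameters and likelihood-ratio statistic LR >= 0,

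AIC(with term) - AIC(without term) = 2k - LR.

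This is the reduction in AIC on removal. Its maximum is 2k, reached only at LR = 0.

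**Three readings.**

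- **A. Stop when the best removal lowers AIC by less than 2.** Removal needs 2k - LR >= 2, so LR <= 2k - 2.
- **B. Drop a term whose presence lowers AIC by less than 2.** Drop if LR - 2k < 2, so the term stays if LR >= 2k + 2.
- **C. Drop whenever removal lowers AIC by less than 2.** Drop if 2k - LR < 2, so LR > 2k - 2.

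Tail areas are from the chi-square distribution with k degrees of freedom, for one term tested once. Plain minimum AIC (keep if LR > 2k) is shown for comparison.

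| k | A: dropped if | A: chance a null term is dropped | B: kept if | B: kept at p <= | C: chance a null term is dropped | Plain AIC: kept at p < |
|---|---|---|---|---|---|---|
| 1 | LR <= 0 | 0 | LR >= 4 | 0.0455 | 1 | 0.157 |
| 2 | LR <= 2 | 0.632 | LR >= 6 | 0.0498 | 0.368 | 0.135 |
| 3 | LR <= 4 | 0.739 | LR >= 8 | 0.0460 | 0.261 | 0.112 |
| 4 | LR <= 6 | 0.801 | LR >= 10 | 0.0404 | 0.199 | 0.092 |

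For k = 1 under reading A the reduction is 2 - LR. With LR = 0.5 it is 1.5, and with LR = 0.01 it is 1.99; both are below 2, so the term stays. Under reading C every one-parameter term with LR > 0 is dropped, and for larger k strong terms are removed while weak ones stay.

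**Numerical check.** 1,000 simulated Poisson data sets with a log-interval offset and one null one-parameter covariate (assumed settings: 3,000 records, baseline rate exp(-2.5)). The largest fall in AIC on removing the null term was 1.999999. Reading A dropped it in 0 of 1,000 sets, reading B in 95.7%, and plain AIC in 85.4%. The bound of 2 does not depend on these settings.

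**Dependence.** Current age = age at diagnosis + diabetes duration. With two of them in the model, the third as a linear term adds no information (LR = 0), and its handling depends on how the software counts the redundant parameter.

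**The case against.** The strongest reply is that reading B is an ordinary working rule, close to p < 0.05, and is probably what was meant. That is fair. The impossibility result belongs to reading A alone, and the fault is that the text does not choose between the readings.

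A reader might go further and infer that the procedure does not select at all. The SAP does not support that. Even under reading A, terms with several parameters can be dropped: smoking, albuminuria and deprivation quintile if entered as factors, and continuous covariates entered with more than one polynomial parameter.

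A reader might also infer that the starting model is wrong, since backward elimination from age, sex and duration could remove only those three. That does not follow either. The initial tabulations use the same three as standard adjusters. The covariate section lists candidates for inclusion, the hidden Markov section refers back to a fuller clinical model, and the performance section speaks of added clinical covariates. The three are best read as a base set within a larger model. What is missing is a sentence saying that all candidates enter first and that the base set is exempt from removal.

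Two further points stand in the plan's favour. Final performance is reported on held-out patients, so retained noise terms would not make it look better than it is. The overlap among the lipid measures is largely handled, because the covariate section already treats them as a set from which a combination is chosen. On the age terms, nothing requires all three to be linear, and a redundant column does not change predicted risk.

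**Conclusion.** The point holds at moderate severity. As a stopping rule on removal, the stated threshold cannot remove any one-parameter term with LR > 0, yet it removes null terms of 2 to 4 parameters with probability 0.63 to 0.80. Across the possible readings, the same sentence runs from keeping every one-parameter term, through keeping those at p <= 0.0455, to dropping them all. This is algebra from the definition of AIC; only the tail areas rely on the chi-square approximation.

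The linear dependence of current age, duration and age at diagnosis is exact, on the assumptions that all three are entered linearly and are derived from the same diagnosis date. Non-linear transforms can break it.

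No effect on AUROC, calibration or screening counts has been shown. With a 70/30 split by patient, the harm is an undefined and possibly overfull model, not optimistic reported performance.

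**What to change.** Replace the selection sentence with wording such as:

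> Start from the model containing every listed covariate that passes the missingness rule, together with the age and sex interactions. Current age, sex and diabetes duration are forced in. At each step remove the non-forced term whose removal gives the lowest AIC. Stop when every remaining removal would raise AIC by 2 or more (LR >= 2k + 2). The same criterion applies in the fractional-polynomial step, with all polynomial parameters counted in k.

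This keeps a one-parameter term at p <= 0.0455 and a four-parameter term at p <= 0.0404, so terms of different size face similar thresholds. Add that age at diagnosis is not entered as a linear term alongside current age and duration.

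The cost is a few sentences of SAP text. It needs no new data and, if made before the models are fitted, no repeat analysis.

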### b. Two-step analysis with multi-state modelling & survival analysis:

We will use hidden Markov models to model the DRS data. The advantages to this approach are that it allows us to model the risk for transition incorporating all available data on prior screening even though individuals have variable number of examinations at differing intervals. It also allows us to model grading misclassification as it separates the 'true but unseen grade' from the 'observed grade'. We will fit separate models by diabetes type and the models will be adjusted for age, sex and diabetes duration. As it is not feasible to extend the multi-state modelling approach to a more complex model that includes many clinical covariates we will "plug in" the risk score computed from the hidden Markov model into the fuller model that includes all available clinical covariates as described above.

**One-step survival analysis:** We will evaluate an alternative approach of not using the hidden Markov model but instead fitting separate models for individuals with 0, 1, 2 or more previous examinations. This is possible as we have a large dataset so that we will have an adequate sample size to learn a predictive model within each of these strata.

**Non-parametric methods:** We shall also evaluate non-parametric methods for interval-censored survival analysis. These kernel-based methods, which make predictions based on a function that evaluates the similarity between pairs of observations, generally outperform simple regression models for prediction though the predictions are not readily explainable.

### Performance evaluation

The performance of the final model will then be reported from the test dataset.

Discrimination will be assessed using a C-statistic (area under the receiver operating characteristic [AUROC]). We will calculate the AUROC within age and sex strata and then take a weighted average of these to define the final AUROC.

Calibration will be summarized using a calibration plot, calibration slope, and Hosmer-Lemeshow test.

We will also report out the net reclassification indices and the IDI. However note that we consider the AUROC to be the most valid of these. Integrated Discrimination Index (IDI). The IDI =  $(IS_{new} - IS_{old}) - (IP_{new} - IP_{old})$  where IS is the integral of the sensitivity across all possible cut-off values for the new ( $IS_{new}$ ) and old models ( $IS_{old}$ ) and IP the corresponding integral of 1-specificity with the new model reflecting the model with added clinical covariates and the old model being based only on the DRS screening data. These metrics will allow us to assess how well these models improve prediction of risk for transition to referable eye disease.

In the test set we will compare the predictive performance of the prediction model with this hidden markov derived measure with the simpler indices of past screening results as described under a. above

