### **Initial tabulations**

For each continuous covariate being considered :

- Summarise its distribution as mean median sd iqr and range and plot its distribution (density or histogram) plot
- Tabulate the frequency of all categorical variables

Events:

- Show the number (%) and event rate of incident events during follow up By AGE and SEX and diabetes type
- By Sex strata and for broad age bands and all ages combined show the age standardised event rate for each of the event of interest standardised to the 2013 European Standard Population

Then with any referable retinopathy as the event of interest :

- Summarise the distribution of follow up time range of person entry and exit dates
- Summarise the distribution of covariates at baseline by subsequent event status

- In the same table show the p value and the beta regression coefficient for the current age - sex -and diabetes duration -adjusted associations of all variables with the outcome

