### Utility assessment

To be expanded: We will compare the estimated number of screenings required to maintain interval disease rate below a given threshold using the maximally predictive model from the above process with a much simpler decision algorithm such as i) the current annual screening for all programme and ii) a programme that would screen all type 1s annually and all types 2s biannually.

Since there are many ways in which policy formulations might utilise prediction risk. We will produce some examples; for instance we can show what the impact on number of screens per annum based on individualised screening intervals set by a series of thresholds of risk (e.g. 1% or 2.5% or 3%). We can also calculate the number of people who will potentially have a delay of >3 months in detection of referable disease and calculate the median 'delay' for each scenario (i.e. the interval between when they would have been screened based on current screening scheme and when they would be screened under the new scheme). The aim is that the models will be able to evaluate a wide range of potential screening policies to provide interactive feedback to policy makers.

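### The only AUROC the SAP defines is averaged within age and sex strata, so it measures discrimination beyond age and sex, not how well the tool ranks the whole screened population

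*SAP*

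**What the plan says.** Under Performance evaluation, discrimination in the test set is assessed by a C-statistic, defined as follows: "We will calculate the AUROC within age and sex strata and then take a weighted average of these to define the final AUROC". No pooled AUROC is mentioned, and neither the age bands nor the weights are given. The nearest hint is under Initial tabulations, where event rates, not AUROCs, are to be shown: "By Sex strata and for broad age bands and all ages combined show the age standardised event rate".

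The same section adds "Calibration will be summarized using a calibration plot, calibration slope, and Hosmer-Lemeshow test", then the net reclassification indices and the IDI, with the remark that "we consider the AUROC to be the most valid of these".

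Age and sex are also predictors. The Poisson regression section states: "We include current age, sex, and diabetes duration as our base set of covariates in our initial model". It adds: "We will also select across age and sex interaction terms for each covariate".

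The Utility assessment sets individual screening intervals by risk thresholds, with 1%, 2.5% and 3% as examples. These thresholds do not vary by age or sex. The population is everyone with diabetes aged 12 or over, and type 1 and type 2 are modelled separately.

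**The concern.** An AUROC is the probability that a randomly chosen case has a higher score than a randomly chosen non-case. Computed within age and sex strata, it compares only people of the same sex and similar age. The tool is used differently: a young and an old patient are held against the same threshold, so the ranking between them matters.

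Objective 2 is to validate prediction performance. A reader who takes the final AUROC as the answer would be told how well the tool discriminates among people already alike in age and sex. That number gives almost no credit to a model that handles age and sex correctly, and it hardly marks down one that leaves them out.

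**Working it through.** **Inputs.** The SAP states no AUROC, effect size, age distribution, band or weight, so there is no planned figure to reproduce. Everything below is assumed: 600,000 person-intervals per scenario; mean event risk 3%; age independent of the other predictors, with mean 65 and SD 12 (type 2-like) or mean 40 and SD 16 (type 1-like); log rate ratio for sex 0.3; log rate ratio per SD of age 0.1 to 0.7; SD of the remaining linear predictor 0.6 unless stated; strata weighted by events.

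**Definitions.** Pooled AUROC = P(score of case > score of non-case) + ½ P(tie), over all pairs. Stratified AUROC = Σ wₛ AUROCₛ / Σ wₛ, over sex × age-band strata s.

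**Sex.** Within a stratum the sex main effect is the same constant for everyone and cancels. The loss is exact: reversing the sex effect on top of a reversed age effect left the stratified value at 0.662 (type 2-like, age effect 0.4, 10-year bands).

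**Age.** Within a band the age term still varies, but little. If ages are roughly uniform in a 10-year band, their SD is 10/√12 = 2.89 years. With 0.4 per 12 years, the age term has within-band SD 0.4 × 2.89/12 = 0.096, against 0.4 in the population, or 0.096/0.4 = 24%. A 20-year band doubles this to 48%.

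**Correct model against a model omitting age and sex** (type 1-like; correct / omitted, difference in brackets):

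| Age effect per SD | Pooled | 10-year bands | 20-year bands | Two bands | Calibration slope |
|---|---|---|---|---|---|
| 0.1 | 0.676 / 0.670 (0.006) | 0.670 / 0.670 (0.000) | 0.670 / 0.670 (0.000) | 0.671 / 0.670 (0.001) | 1.00 / 0.99 |
| 0.2 | 0.682 / 0.669 (0.013) | 0.670 / 0.670 (0.000) | 0.671 / 0.670 (0.001) | 0.673 / 0.670 (0.003) | 1.00 / 1.01 |
| 0.4 | 0.704 / 0.670 (0.034) | 0.672 / 0.671 (0.001) | 0.675 / 0.671 (0.004) | 0.682 / 0.671 (0.011) | 1.02 / 1.02 |
| 0.7 | 0.752 / 0.674 (0.078) | 0.680 / 0.676 (0.004) | 0.686 / 0.676 (0.010) | 0.709 / 0.675 (0.034) | 1.00 / 0.99 |

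With other-predictor SD 1.0 and age effect 0.4, the pooled difference is 0.789 − 0.771 = 0.018 and the 10-year stratified difference is 0.773 − 0.773 = 0.000.

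**Age SD 12, age effect 0.4, 10-year bands.** Stratified 0.668 / 0.666; pooled 0.698 / 0.665. A repeat run under the same effects gave 0.671 / 0.670 and 0.702 / 0.668.

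**Does calibration show the difference?** In the first of these two runs the slopes were 0.965 and 0.967, and observed/expected by decile of predicted risk ran 0.97–1.13 for the correct model and 0.97–1.11 for the other. In the repeat run both slopes were 0.99. Yet by age the model without age and sex had observed/expected 0.50 below 50 and 1.83 at 80 and over (about 0.5 and 1.85 in the repeat). Slope and decile plot average over age and so miss this.

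**Age and sex alone** (type 2-like, effect 0.4): 0.621 pooled, 0.526 in 10-year bands.

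**The case against.** A covariate-adjusted AUROC is an accepted measure. When the compared models share age and sex terms, it isolates what the other predictors add and is not inflated by the age spread of the population. The hidden Markov model is adjusted for age, sex and duration, and its score goes into the fuller model, so the SAP's main comparison with simpler screening-history indices is largely of this kind. This stands, and is why the stratified value should be kept.

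Three stronger readings are tempting, and the SAP does not support them.

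- *That the measure is blind to age.* It is blind only to the sex main effect. For age the answer depends on band width, which is not stated; with two bands and an effect of 0.7 per SD, correct and age-reversed models differ by 0.165 (type 2-like). Age and sex interactions also still change the ranking within strata.
- *That a model with the age effect reversed would pass unnoticed.* With 10-year bands and effect 0.4 it does score 0.662 against 0.669 for the correct model (type 2-like), but its calibration slope is 0.40 instead of 1. The planned calibration work would show the error.
- *That a distorted model would win the model choice.* The Utility assessment speaks of the maximally predictive model from the whole process and names no single criterion. The remark on validity follows the NRI and IDI and need not place the AUROC above calibration. AIC selection on the full likelihood guards the regression models against dropping a real age effect. The IDI as written is not stratified, so it can respond to age and sex.

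These safeguards leave the main point untouched. The one AUROC that will be reported does not describe ranking across the population, and the candidates need not treat age alike: they include kernel methods and separate models by number of previous examinations, and the IDI's old model rests on screening data only.

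**Conclusion.** The point holds as a gap in how discrimination is reported. The final AUROC removes all discrimination due to the sex main effect and, with bands of about 10 years or narrower, most of that due to age, so it cannot by itself support a statement about how the tool ranks the screened population.

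With an age effect of 0.4 per SD, other-predictor SD 0.6 and 10-year bands, losing age and sex altogether costs about 0.03 of pooled AUROC but at most 0.002 of stratified AUROC, with no visible change in calibration slope. Across the assumed age effects of 0.1 to 0.7 per SD, the pooled cost runs from 0.006 to 0.078 (type 1-like). All of this rests on assumed effects, age distributions, bands and weights. If the true age effect is weak the practical difference is small, and broad bands would make the stratified value partly sensitive to age. Because the SAP fixes neither bands nor weights, the final AUROC is also not fully determined.

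**What to change.** Under Performance evaluation:

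- Report the pooled (unstratified) test-set AUROC within each diabetes type as the measure of overall discrimination, and use it when comparing models that handle age or sex differently.
- Keep the stratified average, label it as age- and sex-adjusted, state its age bands and weights, and use it to compare models that share age and sex terms.

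The cost is a sentence or two in the SAP and a few lines of code, with no new data. The downside is that the pooled value partly reflects the age spread of the population and so travels less well to a population with a different age range. Reporting both values side by side deals with this.

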**13.01.17**

## **Aims**

We aim to develop risk prediction tools that can be used by retinopathy screening services to define the optimal interval to next screening in the national screening programme taking into consideration past screening records and other covariates available in SCI-DM

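### Calibration has no numerical measure of how far predicted risk is off near the absolute risk thresholds; add observed/expected ratios in risk bands, by diabetes type

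*SAP*

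**What the plan says.** Under Performance evaluation, the SAP plans three calibration outputs: "Calibration will be summarized using a calibration plot, calibration slope, and Hosmer-Lemeshow test". They come from the hold-out sample: "The performance of the final model will then be reported from the test dataset". No O/E ratio, calibration intercept or calibration-in-the-large is named anywhere. The other measures are the AUROC, the net reclassification indices and the IDI, and the SAP regards the AUROC as the most valid of these.

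The hold-out is described under Poisson regression: "All model fitting will be done on 70% of the data (selected randomly by patient, maintaining ratio of events". The remaining 30% is used for internal validation. The Objectives call for separate models for type 1 and type 2 diabetes.

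The tool is meant to "define the optimal interval to next screening in the national screening programme" (Aims). Under Utility assessment the plan compares policies by the "estimated number of screenings required to maintain interval disease rate below a given threshold", and offers as an illustration "individualised screening intervals set by a series of thresholds of risk (e.g. 1% or 2.5% or 3" (all percentages).

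**The concern.** A rule that sets an interval when predicted risk reaches a stated percentage uses the level of the prediction, not only its ranking. A reader of the results will want to know what true risk corresponds to a predicted 2.5%, and how precisely that is known.

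Neither numerical calibration summary answers this. The slope describes whether predictions are too spread out or too compressed, and is silent on level. Hosmer-Lemeshow returns a p value without size or direction. The AUROC is also unchanged when all risks are multiplied by one factor. The answer is therefore left to the plot, for which no figure or interval is planned. With separate models by diabetes type, test sets of different sizes are likely, and the same p value would then mean different things in each.

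**Working it through.** The SAP gives no calibration figure, row count or event count, so there is no figure of its own to reproduce. The inputs taken from it are the three calibration outputs, the 70/30 event-matched split and the example thresholds. All other inputs below are assumptions.

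**1. Slope.** If the predicted rate is f times the true rate, then log(predicted) = log(true) + log f. The constant goes into the intercept and the slope stays at 1. This is algebra and needs no assumption about the risk distribution. Simulation agrees (complementary log-log risk, log-rate normal with mean −4 and SD 1, mean risk about 2.9%, 2,000 to 60,000 rows, 40 replicates each): for f from 0.67 to 1.5 the mean slope was 0.97 to 1.04. In the same runs O/E recovered the shift: about 0.80 to 0.84 for f = 1.25, and 1.46 to 1.51 for f = 0.67.

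**2. Hosmer-Lemeshow.** Assume mean row risk 2%, log-SD 1, 10 groups, 10 df and the 5% level. If true risk is r times predicted, the non-centrality is roughly (r − 1)² × expected events, and slightly more when summed over the ten groups.

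| r | Rows | (r − 1)² × expected events | Probability of rejection |
|---|---|---|---|
| 1.05 | 100,000 | 0.0025 × 2,000 = 5 | 28% |
| 1.05 | 200,000 | 0.0025 × 4,000 = 10 | 57% |
| 1.05 | 500,000 | 0.0025 × 10,000 = 25 | 96% |
| 1.20 | 10,000 | 0.04 × 200 = 8 | 45% |

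A 5% error is almost always rejected in a very large set, while a 20% error is missed more often than not in a small one.

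**3. What an error in level does at a threshold.** True risk = 1 − exp(−r × −ln(1 − 0.025)). For r = 1.2 this is 1 − exp(−1.2 × 0.02532) = 2.99%, so a nominal 2.5% would really be about 3.0%.

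**4. How much overall error this hold-out would show.** A log-link Poisson model with an intercept has observed = expected in its training data. In 60,000 simulated rows at 2.9% risk, split 70/30 without matching on events, test O/E had mean 1.006 and SD 0.049. That agrees with √(1/522 + 1/1,218) = 0.052, from 18,000 × 0.029 = 522 test events and 42,000 × 0.029 = 1,218 training events. With the event ratio maintained, as the SAP specifies, a simulation gave mean 1.000 and SD 0.007. An overall error of 20% is thus not a realistic expectation for this model in this test set.

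**5. Error confined to risk bands.** An overall ratio near 1 does not settle the matter. In an assumed misspecified model, overall O/E and slope were both about 1.0, while O/E was 0.88 for predicted risks of 2–3.5% and 1.26 below 1%. A predicted 2.5% would then be about 0.88 × 2.5 = 2.2%, and a predicted 0.8% about 1.26 × 0.8 = 1.0%. This shows what can happen; it does not forecast what will.

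**6. Precision of the proposed measure.** The 95% half-width of O/E is about 1.96/√events: 1.96/√1,000 = 6% with 1,000 events, and 1.96/√100 = 20% with 100 events in a band.

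**The case against.** The strongest reply has four parts.

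*The plot is planned.* A reader might infer that the plan is blind to uniform over- or under-prediction. It is not: the plot is the first item listed, and a uniform error appears there as points lying to one side of the diagonal, with direction and approximate size. This stands. What is missing is a number with an interval beside the plot.

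*The design largely excludes a uniform error.* Step 4 bears this out. The hidden Markov score does not change it, because that score is entered into the fuller covariate model, which again has an intercept. The overall ratio is therefore informative mainly for the kernel methods, an alternative link or a penalised fit, all of which the SAP leaves open. Nor would a random split reveal drift in later calendar years. This also stands, and it moves the weight from the overall ratio to the risk bands.

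*The thresholds are examples.* A reader might take 1%, 2.5% and 3% as the screening rule, and conclude that a uniform error would shift every interval by the same factor. Utility assessment is marked as still to be expanded, and the figures are illustrations. How intervals would be assigned is not fixed, and with discrete choices many patients would not move. The weaker statement survives: any policy of this type acts on absolute risk.

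*Hosmer-Lemeshow looks at misfit across risk groups, which an overall ratio cannot.* True, so removing it is not essential. Banded ratios cover the same ground and give size and direction.

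**Conclusion.** The point holds as a cheap improvement. The SAP quantifies neither the size nor the direction of error in absolute risk, although its utility assessment relies on absolute risk. The insensitivity of the slope to a uniform factor is exact. The dependence of the Hosmer-Lemeshow p value on sample size is general; the particular probabilities (28% to 96% for a 5% error, 45% for a 20% error at 10,000 rows) rest on assumed risks and row counts. The 0.88 and 1.26 band ratios come from one assumed misspecification.

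The documents do not support the claim that the model will be materially miscalibrated overall, or that the planned outputs would hide such an error: the plot is there, and the split keeps the overall ratio close to 1 for the main Poisson model. The gap is the lack of an estimate with an interval in the range of risk where decisions would be made.

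**What to change.** In Performance evaluation, add the O/E ratio with a 95% interval in the test set, separately for type 1 and type 2. Report it mainly in predicted-risk bands around whichever thresholds the utility assessment uses, with bands defined on the same risk, over the same time horizon, as the threshold. Choose the bands in advance and wide enough for useful precision, given step 6.

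Report the overall ratio as well, with a note that the event-matched split holds it near 1 for a Poisson model with an intercept, so that it is informative mainly for kernel, alternative-link or penalised models.

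Keep the plot and slope, and base the calibration conclusion on these and the ratios. The Hosmer-Lemeshow p value may be dropped or kept as secondary.

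The cost is a sentence or two of SAP text, simple programming and a few more table rows. The convenience of a single p value as the summary is lost.
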